### **Health and nutritional education**

Education on nutrition, health and hygiene will be provided in group sessions to all caretakers of eligible children on a regular basis. The content of nutrition education sessions will be based on locally available material, but adapted according to formative research carried out during the pilot study conducted in February 2013 where information of food availability and food consumption was collected.

In addition, caretakers of children allocated to the LNS and the iCSBS groups will receive specific recommendations according to the food to be taken by the child (frequency, timing, and, for the iCSBs groups, preparation and cooking).

### **Medical treatments**

At inclusion, all children will benefit from:

- Measles vaccination, if there is no evidence of previous vaccination
- Treatment against intestinal parasites (200 mg of Albendazole for children of 4 to 8 kg; 400 mg for children of more than 8 kg).
- Diagnosis of malaria with systematic treatment based on Artesunate-Amodiaquine (following National Guidelines) in case of positive results to the rapid test.

---

 Children vaccinated at 6 months would receive a second injection at 9 months.

- Vitamin A supplementation (100 000 UI for children of 4 to 8 kg; 200 000 UI for children of more than 8 kg), if there is no evidence of vitamin A supplementation in the previous month.

(See annex 5)

A nurse will examine the children at inclusion and at each fortnightly (3 months of intervention) or monthly follow-up visit (3 months of follow-up) for a total of 6 months and any disease diagnosed will be treated following National Guidelines. Parents/guardians will be encouraged to bring their children to the clinic any time if the child is ill for medical assessment and appropriate treatment.

### Incentives

All caretakers will receive a mosquito net at admission and a bar of soap every other week. At the end of the study (after 6 months), incentives will be given to all participants (likely clothing and a cooking pan). At the baseline, 3 months and 6 months follow-up visits (that is visits requiring the presence of the child during the majority of the day), children and caretakers will be provided with a meal and with activities during the waiting time (i.e knitting activities or others for the mothers and toys for the children). For evaluation of the level of physical activity, the children will be given a t-shirt to wear over the accelerometer, which can be kept after the study period.

#### 3.1.4. Study design

Figure 3 Trial design

|          |                         | Dry skimmed milk (% mass / %protein) |       |        |    |
|----------|-------------------------|--------------------------------------|-------|--------|----|
|          |                         | 0%                                   | 8/20% | 20/50% |    |
| R | CSB/Dehulled soy | a                                    | b     | c      | 1. |
|          | CSB/Soy isolate  | d                                    | e     | f      |    |
|          |                         |                                      |       |        |    |
|          | LNS/Dehulled soy | g                                    | h     | i      | 2. |
|          | LNS/Soy isolate  | j                                    | k     | l      |    |

 Children with moderate anemia (hemoglobin concentration <9gdl) would first receive treatment for possible associated infections. Hemoglobin concentration (Hemocue) would be assessed at the next visit and closely followed-up. Iron and folic acid supplementation would be considered if hemoglobin level does not improve with food supplementation and in the absence of associated infections.

Children will be randomized to either an iCSBs or a LNS intervention. Children randomized to the iCSBs arm will be further randomized to one of the 6 iCSBs: based either on dehulled soy or on soy isolate and containing either 0%, 20% or 50% of proteins provided by DSM. Similarly, children randomized to the LNS arm will be further randomized to one of the 6 LNS: based either on dehulled soy or on soy isolate and containing either 0%, 20% or 50% of total protein provided by DSM.

### 3.1.5. Outcomes and adverse events

#### **Efficacy**

- Primary outcome: absolute lean-mass increment (in kg) from baseline at 3 months using deuterium dilution technique.
- Secondary outcomes lean-mass increments in kg/cm and in g/kg/day, increase of WHZ to >-2, linear growth, MUAC, level of physical activity, development in motor and language milestones, thymic size, morbidity (e.g. malaria, severe anemia, severe acute malnutrition, diarrhea, respiratory infection, hospitalization, death), hemoglobin concentration, serum acute phase proteins, IGF-1, serum ferritin and whole blood concentrations of essential fatty acids.

#### **Safety**

Adverse events (AE): Although we do not expect the foods to cause any harm, peanut, milk, and soy proteins can be allergenic. AE could include: digestive symptoms (diarrhea and/or vomiting), cutaneous symptoms (hives) and, respiratory symptoms (wheezing) within one hour after ingestion of the food. The first dose of the products will be taken under observation and anaphylactic kits will be available at each recruitment sites, where the study nurse will be trained in how to respond to any allergic reaction. All signs of possible allergic reaction will be recorded as part of the fortnightly morbidity assessment, and will be treated accordingly. Serious AE related to this study could include: angioedema, anaphylactic reaction, and death. All serious AE will be immediately communicated to the trial manager who will ensure that they are addressed in an appropriate and timely manner and reported to all study investigators and trial sites, according to Good Clinical Practice. The trial manager will be responsible for the medical management of all adverse events, and will ensure referral to the national health system if necessary, including follow-up.

---

 Definition of the ICH-GCP glossary: Adverse Event : Any untoward medical occurrence in a patient or clinical investigation subject administered a pharmaceutical product and which does not necessarily have a causal relationship with this treatment. An adverse event (AE) can therefore be any unfavorable and unintended sign (including an abnormal laboratory finding), symptom, or disease temporally associated with the use of a medicinal (investigational) product, whether or not related to the medicinal (investigational) product. Serious Adverse Event (SAE): Any untoward medical occurrence that at any dose: results in death, is life-threatening, Requires inpatient hospitalization or prolongation of existing hospitalization, results in persistent or significant disability/incapacity, or is a congenital anomaly/birth defect.

Furthermore the national ethical review board will be notified and will be asked to advise the investigators of future actions to be taken.

In addition, any possible untoward medical event possibly related to the investigations conducted in this study (i.e. tracer dilution test, blood sampling) will also be collected during the investigation itself and as part of the morbidity assessment. Any research related conditions will be managed according to National Guidelines

### 3.1.6. Study withdrawals and referrals

Withdrawals will not be replaced. The reasons for withdrawal or switch to RUTF and their consequences on further intervention and follow-up are described in the Table 1.

**Table 1. Reasons for withdrawal or referral.**

| Reasons for withdrawal                                                        | Further nutritional supplement         | Further follow-up                                                                   | Further assessment                                                                                                             |
|---------------------------------------------------------------------------------------------------------|------------------------------------------------------|---------------------------------------------------------------------------------------------------|----------------------------------------------------------------------------------------------------------------------------------------------|
| Withdrawals                                                                               |                                                      |                                                                                                   |                                                                                                                                              |
| Spontaneous withdrawal of consent                                                                       | None                                                 | None                                                                                              | None                                                                                                                                         |
| Defaulters (having missed 2 consecutive visits), visited at home and not keen to come back in the study | None                                                 | Home visit : referral to the ATFC or health center in case the child developed SAM or any illness | - Life and nutritional status at the home visit.
- Reasons for defaulting.                                                                |
| Lost to follow-up (having missed 2 consecutive visits, visited at home but not possible to locate)      | None                                                 | None after unsuccessful home visit                                                                | None                                                                                                                                         |
| Serious Adverse Events                                                                                  | Local Foods                                          | Until the end of treatment                                                                        | - Outcome of the treatment
- Anthropometric measurements and clinical assessment until end of treatment                                   |
| Other                                                                                     |                                                      |                                                                                                   |                                                                                                                                              |
| Transfer to the ATFC or ITFC,                                                                           | RUTF or food as provided at the ITFC or the hospital | Until the end of treatment                                                                        | - Outcome of the treatment
- Anthropometric measurements and clinical assessment until end of treatment                                   |
| Hospitalization                                                                                         | Continue intervention                                | Until the end of treatment                                                                        | - Medical follow-up
Outcome of the treatment
- Anthropometric measurements and clinical assessment until end of treatment  |

 Participants who withdraw informed consent or were lost to follow-up will not receive further incentives. Other participants will receive the incentives according to the planned timing at the start of the study.

 Children receiving other nutritional intervention (which is not part of Study) after being referred, they will be considered as failure to respond to treatment, and data obtained after receiving other nutritional intervention than previewed will not be included for data analysis

Appropriate free care, including referral when needed, will be ensured by the study team and ALIMA to children who develop SAM during the study. Children diagnosed with other diseases during the study will be referred for relevant treatment. Referral and treatment within the scope of care of the national health system in Yako will be provided free of care.

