### *3.1.3. Interventions: food products and quantities, medical treatment and incentives*

#### **Food products and quantities**

Children will receive 500 kcal/day. Food will be distributed fortnightly during a 3 month period. At each visit, a ration will be given on the spot. Mothers will be asked to bring back the empty LNS packs at the next visit to give to the personnel charge of the supplement (not to staff involved in measurements, to ensure blinding).

CSB will be provided in bi-weekly rations, to be prepared at home.

During the entire follow-up, any child developing severe acute malnutrition (WHZ less than – 3 z-scores, MUAC <115 mm or edema) would be referred for treatment of SAM. The following children will be referred to Yako pediatric unit, which is supported by ALIMA, for medical evaluation;

- Children admitted based on WHZ  $\geq$  -3 - and < -2 z-scores who have not reached a WHZ  $\geq$  -2 z-scores at the end of the 3 months intervention
- Children admitted on MUAC  $\geq$  115mm and < 125 mm who have not reached 15% weight gain,
- Children presenting a weight loss  $\geq$  5% from his/her weight at baseline for two consecutive visits.

Should these children receive other nutritional intervention during their hospitalization, they will be withdrawn from the study as failures to respond to treatment. Data obtained after receiving other nutritional intervention than previewed will not be included for data analysis.

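### Table 1 gives opposite product instructions for a child admitted with intercurrent illness, because the protocol's own definition makes that admission a serious adverse event

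*Combined protocol and SAP*

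**What the plan says.** Section 3.1.6 makes Table 1 the operative rule: "The reasons for withdrawal or switch to RUTF and their consequences on further intervention and follow-up are described in the Table 1". Three of its rows matter here.

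- "Serious Adverse Events" is the last row of the Withdrawals block. The onward supplement is local foods. Assessment consists of the outcome of treatment, anthropometry and clinical review until treatment ends.
- Hospitalization is in the block headed Other. The supplement entry is "Continue intervention". Medical follow-up is added to the same kind of assessment list.
- Transfer to the ATFC or ITFC is also under Other, with RUTF or whatever food the ITFC or hospital provides.

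The Safety part of section 3.1.5 carries a footnote with the ICH-GCP glossary definitions. An adverse event there need not be caused by the product. A serious one includes any untoward occurrence that "Requires inpatient hospitalization or prolongation of existing hospitalization". The main text of the same part adds examples: "Serious AE related to this study could include: angioedema, anaphylactic reaction, and death".

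Section 3.1.13 restricts the primary analysis to randomised children with both a baseline and a 3-month lean mass measurement. Table 2 schedules the deuterium test at months 0 and 3 only.

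**The concern.** Two operative rules cover the same event and cannot both be followed. Admissions are expected in this trial: the morbidity outcomes in section 3.1.5 include "severe acute malnutrition, diarrhea, respiratory infection, hospitalization, death". When a child is admitted with an intercurrent infection, one row withdraws the child from the product and the other continues it.

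Two things are at stake. The first is consistency: the same event can be recorded as a withdrawal in one child and as continued intervention in another, so withdrawal counts by group would partly reflect which row was consulted. The second is the primary outcome. Lean mass is measured only twice, so a child without the month 3 deuterium test leaves the primary analysis. For a child handled under the serious adverse event row, nothing in Table 1 secures that test.

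**Working it through.** No figure in the plan depends on this point, so the check sets the texts side by side.

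1. *Does an admission count as a serious adverse event?* Under the section 3.1.5 footnote, yes, when it is for an untoward medical occurrence. The definition sets no condition on relatedness to the food.

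2. *What does Table 1 then instruct?*

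| Row | Block | Product | Listed assessment |
|---|---|---|---|
| Serious adverse event | Withdrawals | Replaced by local foods | Treatment outcome, anthropometry, clinical review |
| Hospitalization | Other | Continued | The same, plus medical follow-up |
| Transfer to ATFC or ITFC | Other | RUTF or facility food | Treatment outcome, anthropometry, clinical review |

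A child admitted for intercurrent illness satisfies the first two rows, and their product entries are opposite.

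3. *Does Table 1 settle the overlap?* No. The first row is not limited to product-related events, and no order of precedence is given. The third row may overlap as well if an ITFC transfer is an inpatient admission; the table does not say.

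4. *Does another rule settle it?* Section 3.1.3 says of children referred for non-recovery or weight loss: "Should these children receive other nutritional intervention during their hospitalization, they will be withdrawn from the study as failures to respond to treatment". Footnote 2 to the Hospitalization row says: "Children receiving other nutritional intervention (which is not part of Study) after being referred, they will be considered as failure to respond to treatment". These two agree with each other, and both apply only once another nutritional intervention has been given. They are not part of the conflict and do not resolve it.

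5. *Is the month 3 lean mass measure secured?* For the serious adverse event row, the listed assessments omit deuterium dilution and stop at an end of treatment that is not defined; it could mean the illness or the supplementation. The child is also classed as withdrawn. The measure is therefore not assured. For the Hospitalization row, the child stays on product and is not classed as withdrawn, so nothing removes the child from the Table 2 schedule.

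6. *Does the sample size change?* No. The plan's figures reproduce: 16 / 0.4² = 100 per cell; 100 / (1 − 0.25) = 133.3, rounded up to 134; 12 × 134 = 1,608. The conflict enters none of these.

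**The case against.** The best defence is that the authors meant something coherent. The Safety text is mainly about food allergy, and its examples of serious events related to the study do not include admission to hospital. Giving Hospitalization its own row outside the Withdrawals block makes most sense if the first row was meant for reactions to the product and the other for intercurrent illness. That may well be the intention. But the examples are introduced as possibilities, the adopted definition disregards causality, and Table 1 carries no such limit. If this is the intended reading, it has to be written in.

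The defence is right about several stronger inferences that a reader might draw.

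- *That hospitalised children lose their 3-month lean mass, so the sickest are selectively removed.* This is not shown. Hospitalization-row children are not listed as withdrawn. Footnote 1 keeps incentives on the planned timetable for everyone except consent withdrawals and losses to follow-up, and section 5 foresees follow-up of all participating children. Only the serious adverse event row leaves the measure in doubt.
- *That handling will differ between LNS and iCSB because the trial is open on that factor.* This is conjecture. Section 3.1.5 makes the trial manager responsible for medical management of all adverse events; that person's blinding to LNS or iCSB is not stated. The soy and milk contrasts within each product type are less exposed, because section 3.1.14 says participants and staff are blind to those contents.
- *That the number affected can be put at some share of 1,608.* An assumed admission rate of 3 to 10% would give 0.03 × 1,608 = 48 to 0.10 × 1,608 = 161 children, but the rate has no source in the documents. The count would also place every admission under both rows, although ATFC and ITFC transfers have a row of their own.

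**Conclusion.** The contradiction stands on the current text. It rests on reading the section 3.1.5 definition as the one that governs the term in Table 1, and the documents offer no other definition. The consequence for the primary analysis is narrower: for children handled under the serious adverse event row, the 3-month deuterium measure is not assured. How many children this concerns, and whether they would be spread unevenly over the groups, cannot be determined from the documents. No loss of power and no bias in a particular direction is demonstrated. It should still be corrected, because two rules that cannot both be obeyed bear on product exposure and on who enters the primary analysis, and the correction is a matter of wording.

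**What to change.** 1. The investigators reconcile the serious adverse event and Hospitalization rows of Table 1 with the definition in section 3.1.5, and state how the ATFC/ITFC transfer row relates to both, so that each event leads to one instruction. Whether the product stops or continues is a clinical decision for them.

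2. Independently of that decision, the Further assessment column states that the scheduled 3-month deuterium and anthropometry visit is carried out for every randomised child whose caretaker still consents, on product or not.

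The cost is table wording, plus tracing and measuring some children who have stopped the product. The visit is already in Table 2 for every child. The change does not bring every such child back into the analysis: data obtained after another nutritional intervention stay excluded under section 3.1.3 and footnote 2 to Table 1. That is a separate rule, which this fix leaves as it is.

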### *3.1.7. Sample size*

In the absence of information on the increase of LBM from 0-3 months among children with MAM in this age group, we assume that a 0.4 SD difference in change/increase in lean body mass between groups as clinically relevant. The sample size per group,  $n$ , required to detect a change,  $d$ , in a continuous variable with standard deviation,  $s$ , with alpha set at 5% and a 80% power, is  $16*s^2/d^2$ . Hence, to detect a 0.4 SD greater increase in lean body mass between 2 products/cells, we will need 100 children in each group. To allow for a 25% expected loss to follow-up/drop-out in the nutritional program in Burkina Faso, we will include 134 children in each of the 12 intervention groups (cells) then  $12 \times 134 = 1608$  children.

Considering a recruitment rate of 54 children with MAM per month per CSPA, the recruitment is therefore expected to last about 6 months and will be limited five CSPA (i.e., 54 children with MAM \* 6 months \* 5 CSPA = 1620 children).

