### 3.1.13. *Data analysis*

The main effectiveness criterion will be the mean change in lean body mass after 3 months of supplementation (absolute increase expressed in kg). The primary analysis will be conducted in the intention to treat (ITT) population and will therefore include all randomized subjects having at least one exploitable baseline and 3 months LBM measures,. The primary analysis will be conducted by means of a single statistical analysis including both main arms, ie LNS and iCSB:

- A three-way analysis of variance (ANOVA) will be used to evaluate if the two interventions modify the effect of dehulled soy and soy isolate at different levels of milk content.
- The ANOVA will also include LBM at baseline as well as a number of additional explanatory (age, sex, MUAC, WHZ, season) that adjust for potential differences present in the study population. To adjust for variation between centers random effects for each centre are also included in the model. Thus, the statistical model will be based on a linear mixed model.
- Pairwise comparisons of means within and across the two arms will be done using the linear mixed model. Multiplicity will be taken into account by adjusting all pairwise comparisons.
- The effect of supplementation, ie. the difference in mean changes in LBM at 3 months of each group will be presented in terms of estimated means with 95% confidence intervals.

All other statistical analyses of the primary endpoint, ie other study populations, sub-group analysis, and inside-the-table comparisons, and all statistical analyses of secondary endpoints, will be considered secondary analyses. These include:

- Evaluation of the effect of the type of soy by comparing, in the LNS and the iCSBs groups separately, the mean increase in LBM at 3 months over the two groups of soy quality (dehulled soy i.e. 3 groups merged, soy isolate i.e. 3 groups merged).
- Evaluation of the effect of the milk protein content by comparing, in the LNS and the iCSBs groups separately, the mean increase in LBM at 3 months over the three groups of milk protein content (i.e. 2 groups merged for each level of milk).
- Analysis might also be conducted among the subgroup of participants presenting these 2 LBM measurements and the per-protocol population (i.e. excluding participants with violation of protocol).

For all secondary analyses, no adjustment for multiplicity is planned.

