### **Summary of changes to the statistical analysis plan:**

Compared to the statistical plan outlined in the protocol, we eventually decided to deviate on two issues:

1) Our primary outcome was fat-free mass accretion over three months, adjusted for length. We have not changed the primary outcome, but decided to do the length adjustment by dividing with length in meters squared, ie expressing fat-free mass accretion as an index. There are several reasons for this: First, we found that dividing by length in meters squared was the optimal adjustment. Second, since children are growing in length, then it is not enough to adjust for baseline length. Using fat-free mass index at both time points enable us to adjust for not only baseline length, but also changes in length over time.

2) We had initially planned to adjust for multiplicity, in case we had to compare 12 groups. However, while this reduces the risk of type 1 errors, it also increases the risk of type 2 errors. We therefore eventually followed standard practice of not adjusting p-values for reduced factorial model. In other words, for the pairwise comparisons within factors in the reduced models no multiplicity adjustments were applied.

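### The 80% power in section 3.1.7 is for one unadjusted cell pair; with the all-pairs adjustment in section 3.1.13, power for a given 0.4 SD pair is about 29–33% before any covariate gain

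*Combined protocol and SAP*

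**What the plan says.** Section 3.1.7 (Sample size) sets the target difference: "we assume that a 0.4 SD difference in change/increase in lean body mass between groups as clinically relevant". It applies the formula n = 16s²/d² per group, "with alpha set at 5% and a 80% power", and concludes that "to detect a 0.4 SD greater increase in lean body mass between 2 products/cells, we will need 100 children in each group". It then inflates for a 25% loss to 134 per cell, 1608 in total. Multiplicity is not mentioned there.

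Section 3.1.13 (Data analysis) describes the primary analysis as a three-way model in a linear mixed framework. It adjusts for baseline lean body mass, age, sex, MUAC, WHZ and season, with random centre effects. It continues: "Pairwise comparisons of means within and across the two arms will be done using the linear mixed model". The next sentence reads: "Multiplicity will be taken into account by adjusting all pairwise comparisons". No adjustment method is named. The merged soy and milk comparisons, made separately in the LNS and iCSB arms, are secondary and unadjusted.

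The summary of changes to the statistical analysis plan reports a later decision: "for the pairwise comparisons within factors in the reduced models no multiplicity adjustments were applied". It says adjustment had been planned in case all 12 groups had to be compared.

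**The concern.** The power statement and the primary analysis refer to different tests. The constant 16 belongs to a single two-sided 5% comparison of two groups, whereas the planned cell comparisons face a stricter threshold because all of them are adjusted together. A reader of 3.1.7 would believe that a 0.4 SD difference between two named products has an 80% chance of being declared. If the real chance is much lower, a non-significant pair could be taken as a sign that two products work equally well, in a trial meant to inform which supplement to use.

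**Working it through.** **Inputs.** From 3.1.7: d = 0.4 SD, SD set to 1, alpha 5%, 100 evaluable per cell, 25% loss, 12 cells. From 3.1.13: all pairwise comparisons adjusted, within and across arms. Two-sided testing is not stated but follows from the constant: 2 × (1.96 + 0.84)² = 15.7, rounded up to 16.

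**The plan's own figures.** 16 / 0.4² = 100 per cell. 100 / 0.75 = 133.3, so 134. 12 × 134 = 1608. The standard error of a cell difference is √(2/100) = 0.1414 SD, so the expected z is 0.4 / 0.1414 = 2.828. Unadjusted power is Φ(2.828 − 1.960) = 80.7%. Everything reproduces.

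**Number of pairs.** 12 × 11 / 2 = 66. The documents do not state this count; it follows from comparing cells both within and across arms.

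**Power for a given 0.4 SD pair, no covariate gain.**

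- Bonferroni: alpha 0.05/66, critical value 3.368. Power = Φ(2.828 − 3.368) = 29.5% (29.2% with t on 1188 df).
- Tukey: studentized range for 12 means and 1188 df, divided by √2, gives 3.275. Power = Φ(2.828 − 3.275) = 32.8%.
- Sidak gives 29.7%. Holm gives 30–31% by simulation.

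**Difference detectable with 80% power.** Tukey: (3.275 + 0.842) × 0.1414 = 0.58 SD. Bonferroni: (3.368 + 0.842) × 0.1414 = 0.60 SD.

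**With covariates.** If the covariates explain a share R² of the variance, the expected z becomes 2.828 / √(1 − R²). The R² values below are assumptions.

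| Assumed R² | Expected z | Bonferroni | Tukey |
|---|---|---|---|
| 0 | 2.828 | 29% | 33% |
| 0.1 | 2.981 | 35% | 38% |
| 0.3 | 3.381 | 51% | 54% |
| 0.5 | 4.000 | 74% | 77% |

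**Merged contrasts planned within each arm, unadjusted, 80% power.** Soy merges three cells per side, 300 v 300: (1.960 + 0.842) × √(2/300) = 0.23 SD. Milk merges two cells per level, 200 v 200: (1.960 + 0.842) × √(2/200) = 0.28 SD. For a 0.4 SD effect, power is 99.8% and 97.9% respectively.

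**The case against.** The best reply is that the plan is less blind than a per-pair figure suggests, and much of that stands.

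- A reader might infer that any real 0.4 SD difference would usually be missed. The documents do not support that. If one product differed from all 11 others by 0.4 SD, the chance of at least one true detection would be about 76% (Holm) to 80% (Tukey), by simulation. If the difference runs along soy or milk as a factor, the merged within-arm comparisons have ample power. But 3.1.7 makes its claim for two products, and per-pair power is the matching quantity.
- A reader might take 29–33% as the power of the trial without conditions. It assumes no covariate gain, while the primary model includes baseline lean body mass and other covariates. That condition must be stated; even at an assumed R² of 0.5 the figure stays below 80%.
- A reader might infer that a weak interaction test decides whether the cells are collapsed. Neither section 3.1.13 nor the summary of changes states such a rule, and the 0.4 SD in 3.1.7 is defined for a difference between groups, not for a three-way difference of differences.
- A reader might add that the unadjusted reduced models inflate the family-wise error. That concerns a different analysis. The number of tests would have to be inferred, and statisticians disagree on whether distinct factorial questions need joint control.

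The later dropping of adjustment covers only within-factor comparisons in the reduced models. The low figure therefore describes the adjusted 12-cell comparisons, not those models. It does not bring 3.1.7 and 3.1.13 into line.

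**Conclusion.** The point holds as a mismatch between the design calculation and the primary analysis, not as an arithmetic error. The 80% belongs to one unadjusted two-cell test, which is not how 3.1.13 treats the cell pairs. Adjusted over 66 pairs, with 100 completers per cell and R² = 0, a given 0.4 SD pair has about 29–33% power, and the detectable difference is about 1.5 times the one the plan calls clinically relevant (0.58 / 0.40 = 1.46; 0.60 / 0.40 = 1.49). The conclusion does not hinge on the unnamed method, since four standard ones give nearly the same answer. The exact percentage does hinge on R², which the documents do not give.

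**What to change.** In 3.1.7:

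- State that the 80% applies only to one unadjusted cell pair.
- Give the power for the adjusted cell pairs: about 30% for 0.4 SD, or 80% for about 0.58–0.60 SD, without covariate gain. If credit is taken for covariates, state the assumed R² and its basis.
- Give the detectable differences for the merged contrasts already planned within each arm: about 0.23 SD for soy and 0.28 SD for milk, both unadjusted.

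In 3.1.13, name the adjustment method, and say that a non-significant adjusted pair is not evidence of no difference. If the analysis has already been done, the same statements belong in the report.

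Optional, and a design preference on which statisticians may differ: contrasts pooled over both arms for soy, matrix and milk, with Holm over the three factors. The stated figures must then match that procedure. At Holm's first step alpha is 0.05/3 and the critical value 2.394. Soy or matrix (600 v 600) needs (2.394 + 0.842) × √(2/600) = 0.19 SD, and a milk pair (400 v 400) needs (2.394 + 0.842) × √(2/400) = 0.23 SD. The unadjusted 0.16 and 0.20 SD should not be quoted beside Holm.

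The cost is a less favourable stated power; no extra children are needed. Keeping 80% for every adjusted pair would instead take 212 (Tukey) to 222 (Bonferroni) completers per cell. That is 283 to 296 enrolled per cell after 25% loss, or 3396 to 3552 in total, and it is not proposed here.
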